
### Follow-Up Procedures

All patients will be identified and followed up using individual identity cards that are unique to every Chinese citizen, enabling unambiguous linkages. Research personnel will regularly perform face-to-face or telephone follow-up at 3, 6, 12, and 24 months after stroke onset. Information, including death, functional status, activity of daily living, cardiovascular or cerebrovascular events, cognitive function, and adherence to secondary prevention recommendation and TCM treatments, will be obtained. Death will be confirmed *via* a death certificate from the local civil registry or from the attended hospital. New cardiovascular or cerebrovascular events leading to rehospitalization will be confirmed by the discharge diagnosis. Suspected recurrent cardiovascular or cerebrovascular events will be determined by the endpoint judgment committee if without hospitalization (Wang et al., 2019).

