### Study Outcomes

In the CASES-TCM study, the distribution of scores on the mRS at the 3-months follow-up, and any recurrent stroke events including ischemic and hemorrhagic stroke (ICH and subarachnoid hemorrhage) within the 12-months follow-up will be set as the primary outcomes. Secondary outcomes, which will be assessed at different follow-up visits, include the following: exposure and adherence to TCM treatment, improvement of neurological deficits, patients’ subjective feelings, death, functional outcome, activity of daily living, cognitive function, composite of new clinical vascular events, and incidence of adverse events. The complete outcomes of the CASES-TCM study are illustrated in Table 2.

**TABLE 2 T2:** The complete outcomes of CASES-TCM study.

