### Statistical Analysis

A statistical analysis plan (SAP) has been developed prior to the initiation of the CASES-TCM registry. All collected observational data will be analyzed descriptively using established statistical methods. The mean, median, standard median, or interquartile ranges will be used to summarized continuous data, while counts or percentages for categorical data. Between-group comparisons will be conducted using parametric tests [one-way analysis of variance (ANOVA) or Student’s t-test] or non-parametric tests (chi-square test, Fisher’s exact test, Kruskal–Wallis one-way ANOVA on ranks, or Mann–Whitney *U* test), as appropriate. As for time-to-event analysis, patients will be censored at their last follow-up assessment when experiencing a clinical event, at the end of study, or at the time of withdrawal from the study. Cumulative clinical events will be reported as Kaplan–Meier estimates. Cox proportional hazards regression methods will be used for hazard ratio calculation at 95% confidence intervals, and the treatment effect will be assessed using the log-rank test. During the analysis, confounding factors will be considered, and multivariable regressions will be conducted with adjustments for potential covariates and the propensity score. If not specified otherwise in the SAP, missing data will not be imputed. Subjects with incomplete data will be included in the analysis and for each variable; the number of subjects with missing data will be reported. Interim analyses comprising descriptive summaries of collected data will be conducted every 6 months. All statistical tests will be two-sided and statistical significance will be set at *p* < 0.05. Statistical analyses will be performed using SAS software version 9.4 (SAS Institute, Inc.).

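### The censoring sentence makes a clinical event a reason for censoring, which contradicts the Kaplan-Meier, Cox and log-rank analyses in the same paragraph and leaves event timing for a primary outcome misstated

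*Protocol article*

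**What the plan says.** In Statistical Analysis, the protocol article gives one rule for time-to-event data: "patients will be censored at their last follow-up assessment when experiencing a clinical event". It names two further censoring occasions, study end and withdrawal. The same section then says that "Cumulative clinical events will be reported as Kaplan–Meier estimates" and that "Cox proportional hazards regression methods will be used for hazard ratio calculation at 95% confidence intervals", with a log-rank test for the treatment effect.

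Under Study Outcomes, "any recurrent stroke events including ischemic and hemorrhagic stroke (ICH and subarachnoid hemorrhage) within the 12-months follow-up will be set as the primary outcomes", together with the 3-month mRS distribution. Table 2 adds, as secondary outcomes, recurrent stroke at 3 and 24 months, a composite of new vascular events, and all-cause mortality. Under Follow-Up Procedures, research personnel carry out "face-to-face or telephone follow-up at 3, 6, 12, and 24 months after stroke onset". Deaths are confirmed by certificate, rehospitalised events by discharge diagnosis, and suspected events without hospitalisation by the endpoint judgment committee.

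**The concern.** The rule names three occasions for censoring. End of study and withdrawal are ordinary ones. Experiencing a clinical event is not: a patient who has the event under analysis has an observed failure time, which is the opposite of a censored one. The sentence makes no exception for the event being analysed and does not restrict the term to other, competing events. It also places the time at the last follow-up assessment and does not mention the date of the event.

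At stake are the event indicator and the event time for the 12-month recurrent stroke outcome and for the secondary event outcomes. This is the only event and censoring rule that the article gives for any of them. It is a rule that is stated, and stated wrongly. It is not a detail left to the SAP, since the section's proviso about the SAP concerns the imputation of missing data and not censoring.

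**Working it through.** The article states no event count, recurrence rate or power for this outcome, so there is no figure of its own to reproduce. The check is of the logic.

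**1. Same term, two roles.** In the censoring sentence, a clinical event ends follow-up as a censored observation. In the next sentence, clinical events are what the Kaplan-Meier curve accumulates. Both cannot hold for the same event.

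**2. Literal application.** Let d_j be the number of events and n_j the number at risk at time t_j.
- Kaplan-Meier: S(t) = Π(1 − d_j/n_j). If every clinical event is coded as censored, all d_j = 0, so S(t) = 1 and cumulative incidence is 0% whatever the true rate.
- Cox: the partial likelihood is a product over events. With none, it is constant in the coefficient and no hazard ratio can be estimated.
- Log-rank: observed and expected events and the variance are all 0, so the statistic is undefined.

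A simulation of 20,000 patients over 12 months bears this out. It assumed 5% withdrawal per year and a recurrence rate of 5%, 10% or 15%; none of these rates is in the documents.

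| Assumed 12-month recurrence | Stroke coded as event: events, KM incidence | Stroke coded as censored: KM incidence |
|---|---|---|
| 5% | 979, 5.0% | 0.0% |
| 10% | 2,007, 10.3% | 0.0% |
| 15% | 2,834, 14.5% | 0.0% |

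The table shows only that the sentence cannot be applied as written. It does not forecast what the study will report.

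**3. Events counted, but timed at an assessment.** The scheduled visits are at 3, 6, 12 and 24 months, so the intervals between them are 6 − 3 = 3, 12 − 6 = 6 and 24 − 12 = 12 months. The phrase *last follow-up assessment* could mean the visit before the event or the visit at which it is found:

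| Month of stroke | Timed at preceding visit | Timed at the visit that finds it |
|---|---|---|
| 1 | no follow-up visit yet | 3 |
| 7 | 6 | 12 |
| 13 | 12 | 24 |

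Either way, event times collapse onto a few scheduled visits. The article does not say which visit is meant.

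**4. Other readings.**
- A comma after *assessment* would still leave the event as a censoring reason.
- Restricting the clause to events other than the one analysed would remove the contradiction, but nothing in the text makes that restriction.

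**The case against.** The strongest reply is that the intent is plain. The following sentences report clinical events as Kaplan-Meier estimates and compute hazard ratios, Study Outcomes defines recurrent stroke as an outcome, and Follow-Up Procedures sets up confirmation and adjudication. On this view *censored* was used loosely for the end of time at risk, and an analyst would count each event at its date. That stands as to intent. A reader might infer that the study will discard its recurrent strokes; the surrounding text does not support that.

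A reader might also infer that strokes in the second year would be dated back to the 12-month visit and inflate the primary outcome by a calculable amount. The documents do not support that either. It requires the assessment to be the preceding visit, where the visit that finds the event is equally possible. It requires recurrence rates that the documents do not give. It also sits badly with Table 2, which separates recurrence within 12 months from recurrence within 24 months. Death certificates and discharge diagnoses would ordinarily carry dates, so substituting a visit date is not forced.

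Two further inferences go too far. Table 1 lists categories of variables only, so it does not show that event dates go uncollected. How death before recurrence is handled does not follow from this sentence and can be left to the SAP.

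What the reply does not do is make the sentence correct. The intended rule has to be reconstructed from its neighbours, and the sentence itself mentions a follow-up assessment but no event date.

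**Conclusion.** The censoring sentence is wrong as written and contradicts its own paragraph, and it bears on a primary outcome. Applied literally, recurrent strokes would not count as events. If they are counted but timed at an assessment, their times are tied to the visit schedule. The probable cause is a drafting error. The conclusion rests on the wording alone and needs no assumed rates. No size of bias can be derived from the documents, and none is claimed.

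**What to change.** Replace the sentence with:

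> The event time is the date of the first qualifying event, which counts as an event. Patients without the event are censored at the earliest of last contact known event-free, withdrawal, or the end of the outcome window (12 months for the primary outcome).

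Confirm that the SAP uses the same rule. The cost is one sentence in the protocol and a check of the SAP against it. The documents show no need to change the design or the follow-up schedule.

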**Follow-up Information**	
Major events	Death; New cardiovascular events; New cerebrovascular events; Adverse events
Adherence to secondary prevention	Antiplatelet agents; Anticoagulants; Lipid-lowering agents; Antihypertensive agents; Hypoglycemic agents
Adherence to TCM treatment	Specific medicine; Proportion of days covered of TCM treatment
Follow-up evaluation	mRS; BI; MMSE

mRS, modified Rankin Scale; NIHSS, National Institutes of Health Stroke Scale; BI, Barthel Index; MMSE, Mini-Mental State Examination; DSSEIS, Diagnostic Scale of Syndrome Elements in Ischemic Stroke; IVT, Intravenous thrombolytic therapy; EVT, endovascular treatment; AIS, acute ischemic stroke; ICH, intracerebral hemorrhage; TCM, traditional Chinese medicine; ECG, electrocardiogram; OCSP, Oxfordshire Community Stroke Project; TOAST, Trial of Org 10172 in Acute Stroke Treatment; SMASH-U, Structural lesion, Medication, Amyloid angiopathy, Systemic/other disease, Hypertension, Undetermined; PRO-Stroke, Patient-Reported Outcome Scale for Stroke.

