**Primary outcomes**
Distribution of scores on the mRS at 3-months follow-up
Recurrent stroke events (ischemic stroke, hemorrhagic stroke including intracerebral hemorrhage and subarachnoid hemorrhage) within 12-months follow-up

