**Secondary outcomes**
Proportion of patients receive TCM treatment within 24 h after admission
TCM treatment duration within 3-months, 12-months, and 24-months follow-up
Change in the NIHSS score between baseline (admission) and discharge (14 days—mean for length of hospitalization for stroke patients)
Patient-Reported Outcomes Scale for Stroke score at discharge (14 days—mean for length of hospitalization for stroke patients)
Proportion of patients with mRS score ≤2 at 3-months and 12-months follow-up
Distribution of scores on the mRS at 12-months follow-up
Proportion of patients with BI score ≥90 at 3-months and 12-months follow-up
Recurrent stroke events (ischemic stroke, hemorrhagic stroke including intracerebral hemorrhage and subarachnoid hemorrhage) within 3-months and 24-months follow-up
Composite of new clinical vascular events within 3-months, 12-months, and 24-months follow-up
MMSE scale score at 3-months, 12-months, and 24-months follow-up
All-cause mortality within 12-months and 24-months follow-up
Incidence of adverse events during the whole study

mRS, modified Rankin scale; TCM, traditional Chinese medicine; NIHSS, National Institute of Health Stroke Scale; BI, Barthel Index; MMSE, Mini-Mental State Examination.

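### Recurrent stroke, an endpoint without death, is to be reported by Kaplan–Meier, which overstates the absolute risk of recurrence when deaths come first

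*Protocol article*

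**What the plan says.** The Statistical Analysis section of the protocol article sets one estimator for every cumulative event figure: "Cumulative clinical events will be reported as Kaplan–Meier estimates". Group comparisons of event times use Cox regression and the log-rank test, with multivariable and propensity-score adjustment. No competing-risk method is named. The censoring sentence reads in part "patients will be censored at their last follow-up assessment when experiencing a clinical event, at the end of study" and goes on to withdrawal; it does not mention death.

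The endpoints concerned are these:

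- Study Outcomes sets as a primary outcome "any recurrent stroke events including ischemic and hemorrhagic stroke (ICH and subarachnoid hemorrhage) within the 12-months follow-up". Table 2 repeats it as a primary outcome and adds recurrent stroke "within 3-months and 24-months follow-up" as a secondary one. Death is not a component.
- Table 2 also lists "Composite of new clinical vascular events within 3-months, 12-months, and 24-months follow-up". The article does not say whether death counts in that composite.
- Death is an outcome of its own: "All-cause mortality within 12-months and 24-months follow-up". Table 1 collects it under major events ("Death; New cardiovascular events; New cerebrovascular events; Adverse events"), and Follow-Up Procedures has it confirmed by death certificate or by the hospital.

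**The concern.** A patient who dies cannot have a later stroke. Kaplan–Meier applied to recurrence alone normally treats that death as censoring, as if the patient were still at risk but unobserved. One minus the curve then describes recurrence in a hypothetical population in which nobody dies, not the share of registered patients who have a recurrence.

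The Discussion presents the registry as a description of outcomes in real-world practice, so the actual share is what readers will want. Patients enter within 7 days of onset (Patient Population) and are followed to 24 months (Follow-Up Procedures), so early deaths fall inside the observation window. The Introduction reports that an earlier national registry linked use of traditional Chinese medicine (TCM) with more recurrence. Absolute recurrence figures from this study will therefore be read closely. The inflation grows with mortality, so groups with different death rates would be inflated by different amounts.

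**Working it through.** **Plan's own figure.** There is none to reproduce: the article gives no recurrence rate, death rate or event count. Every rate below is an assumption.

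**Direction.** Let h1(u) be the hazard of recurrence and h2(u) the hazard of death without recurrence, with cumulative hazards H1 and H2.

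- One minus Kaplan–Meier, deaths censored: ∫ exp(−H1(u)) h1(u) du.
- Actual cumulative incidence: ∫ exp(−H1(u) − H2(u)) h1(u) du.

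The second integrand is the first multiplied by exp(−H2(u)), which is at most 1. The Kaplan–Meier figure is therefore never the smaller of the two. They are equal only if no death occurs while recurrence is still possible. No outside rate is needed for this.

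**Size at 12 months, constant hazards.** Inputs: assumed Kaplan–Meier recurrence R = 10%; assumed mortality D = 10% to 50%, with the same death hazard before and after a recurrence.

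h1 = −ln(1 − R), h2 = −ln(1 − D), cumulative incidence = h1/(h1 + h2) × [1 − (1 − R)(1 − D)].

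Example with D = 30%: h1 = 0.1054 and h2 = 0.3567, so h1/(h1 + h2) = 0.228. The bracket is 1 − 0.9 × 0.7 = 0.37. The product is 0.0844, or 8.4% against a reported 10%.

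**Size at 12 months, early deaths.** The same totals, but with 70% of the death hazard and 25% of the recurrence hazard placed in month 1. The formula is applied to month 1 and then to months 2–12 among those still alive and recurrence-free. With D = 30%, month 1 contributes 0.0230 and months 2–12 contribute 0.0547, together 7.8%.

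| Assumed 12-month mortality | Actual incidence, constant hazards | Overstatement | Actual incidence, early deaths | Overstatement |
|---|---|---|---|---|
| 10% | 9.5% | 0.5 points (5% relative) | 9.3% | 0.7 points (8%) |
| 20% | 9.0% | 1.0 (11%) | 8.5% | 1.5 (17%) |
| 30% | 8.4% | 1.6 (19%) | 7.8% | 2.2 (29%) |
| 40% | 7.9% | 2.1 (27%) | 7.0% | 3.0 (43%) |
| 50% | 7.3% | 2.7 (38%) | 6.2% | 3.8 (62%) |

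A simulation of the constant-hazard case at 40% mortality gave 7.90%, against 7.87% from the formula. With a Kaplan–Meier recurrence of 5% and constant hazards, the actual incidence is 4.75% at 10% mortality, 4.2% at 30% and 3.9% at 40%, so the relative overstatement is about the same.

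**Two groups.** Give both groups the same recurrence hazard (Kaplan–Meier 10% each) but mortality of 10% and 40%. The curves show no difference. The actual incidences are 9.5% and 7.9%, a difference of 1.6 points that the Kaplan–Meier figures hide. The cause-specific hazard ratio is 1 and is correctly estimated by Cox regression with deaths censored.

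**The case against.** **The detail may be in the unseen SAP.** The article says a SAP exists, and competing-risk handling is often placed there. But this is a stated estimator, not a silence. The same section makes its missing-data rule subject to the SAP and attaches no such proviso to the Kaplan–Meier sentence. The sentence is generic and suits all-cause mortality, but its wording also takes in the primary recurrence endpoint. Crude percentages may be reported as well; that softens the point without removing it.

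**Censoring of deaths is inferred.** This is true: the censoring sentence does not name death. For an endpoint that excludes death, however, censoring is the usual way Kaplan–Meier handles it. Nothing in the text suggests an alternative, such as keeping patients who died in the risk set to the end of the window.

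**The effect may be small.** This is also true at low mortality: at 10% deaths the gap is half a point on 10%.

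A reader might also infer more than the documents support:

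- *That ICH is worst affected.* This follows only if ICH mortality exceeds that of ischemic stroke. It is a reasonable assumption, but the article gives no mortality for either subtype. Likewise, nothing shows that non-users of TCM die more often.
- *That the treatment comparison is biased.* The article compares groups by Cox and log-rank, which with deaths censored are valid for the cause-specific hazard. Only absolute risks and differences taken from the curves are distorted.
- *That the overstatement is typically about 40%.* One route is to carry a constant 30% yearly death risk to 24 months (Kaplan–Meier 9.8% against 7.0%, starting from 5% at 12 months). That implies 1 − 0.7² = 51% dead by then. Another is 1/0.7 = 1.43, the limiting case in which every death precedes every recurrence. Neither is a central estimate.

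**Conclusion.** The point holds as a mismatch between a stated estimator and its endpoint. Followed as written, the plan gives cumulative recurrence figures that cannot be too low and will be too high to the extent that deaths precede possible recurrences. The direction is certain once deaths are censored.

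The size depends on mortality and timing, which the documents do not give. For a 12-month Kaplan–Meier recurrence of 10%, it runs from about half a point at 10% mortality to about 2 points at 40% under constant hazards, and to about 3 points at 40% if deaths come early. It would be smaller if recurrences mostly came before deaths.

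The vascular composite is affected only if death is not one of its components, which the article leaves open. Kaplan–Meier for all-cause mortality is sound.

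**What to change.** Amend the Kaplan–Meier sentence, and the SAP to match, as follows:

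- Report recurrent stroke at 3, 12 and 24 months as Aalen–Johansen cumulative incidence with death as a competing event, overall and separately for ischemic stroke and ICH.
- Do the same for the vascular composite only if death is not a component, and state whether it is.
- Label the Cox hazard ratios for these endpoints as cause-specific.
- Keep Kaplan–Meier for all-cause mortality and for any composite that includes death.
- Say in the censoring sentence how death is handled for each endpoint.

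The cost is small. Death is already ascertained, so no new data are needed, and the estimator is standard in the SAS 9.4 software the article names. The price is slightly lower reported recurrence rates and a little more analysis work.

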TCM has been applied in stroke treatment for thousands of years in China (Chan, 2014). TCM is popularized with wide acceptability, and results of the China Quality Evaluation of Stroke Care and Treatment study, which examined the clinical practice and secondary prevention of stroke in China, indicated that TCM accounted for 83.1% of AIS medication treatment and 42% of ICH treatment (Group of the China Quality Evaluation of Stroke Care and Treatment, 2009; Wei et al., 2011). Additionally, deemed as a part of TCM, acupuncture for stroke treatment has been used in China for over 1,000 years and is increasingly practiced in some western countries (Wu et al., 2006; Zhang et al., 2015).

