## Methods and Design

### Study Design

The CASES-TCM study (registered with ClinicalTrials.gov, Unique identifier: NCT04921397) is a prospective, multicenter, observational disease registry, attempting to depict major clinical characteristics of stroke in patients treated with TCM and to explore any difference in the comparison with other non-TCM user cohorts and the effectiveness and safety of TCM. An overview of this study flowchart is shown in Figure 1. The registry protocol was approved by the institutional review board of the leading center, Dongzhimen Hospital, Beijing University of Chinese Medicine, Beijing, China (No. 2021DZMEC-024-02), and will be approved by the local institutional review boards of all participating sites.

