### Specific Treatment

Different kinds of TCM treatment for patients with stroke will be included because we will focus on whether doctors use TCM based on individual syndrome differentiation, which is etiology in view of TCM theory. We will record TCM application settings including prehospital stage (at home or ambulance), in-hospital stage (emergency department or neurology ward), and hospital discharge (community or at home), and TCM formulations including Chinese patent medicine (injection or oral agents), and TCM compounds. The initiation time of TCM administration for patients with stroke and adherence to TCM treatment will also be recorded. As for other routine treatments, doctors will treat patients with stroke according to the corresponding Chinese guidelines (Chinese Society of Neurology, 2018; Chinese Society of Neurology, 2019). The common management methods include basic control of risk factors, intravenous thrombolysis, mechanical thrombectomy, antiplatelets, anticoagulants, and neuroprotective agents. Additionally, doctors will determine the treatment strategies based on their clinical experience and the patients’ condition when no guideline-recommended therapies are applicable.

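### The plan assigns the test of the treatment effect to an unadjusted log-rank test and does not tie that test to the adjusted model

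*Protocol article*

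**What the plan says.** The Study Design section of the protocol article states that CASES-TCM "is a prospective, multicenter, observational disease registry". One of its aims is "to explore any difference in the comparison with other non-TCM user cohorts and the effectiveness and safety of TCM". Nobody is randomised. Under Specific Treatment, the use of TCM is a matter for the treating doctor: "we will focus on whether doctors use TCM based on individual syndrome differentiation".

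The Statistical Analysis section gives the time-to-event methods in one sentence with two halves. For estimation, "Cox proportional hazards regression methods will be used for hazard ratio calculation at 95% confidence intervals". For the test, "the treatment effect will be assessed using the log-rank test". No stratification factor or weighting is attached to the test. The following sentence says that confounding will be considered and that "multivariable regressions will be conducted with adjustments for potential covariates and the propensity score".

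The time-to-event primary outcome is recurrent stroke within 12 months. The other primary outcome is the 3-month mRS distribution. Patients with AIS and patients with ICH enter the same registry. On how TCM use varies by stroke type, the Introduction cites an earlier survey in which "TCM accounted for 83.1% of AIS medication treatment and 42% of ICH treatment".

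**The concern.** A log-rank test without stratification or weights compares the groups as they stand. It is a valid test of a treatment effect when the groups are comparable apart from treatment, and nothing in this design makes them so. If users and non-users differ in a factor that also drives recurrence, the test responds to that factor.

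The adjusted regressions do not settle the matter, because the text does not say that they supply the test. As written, one question can receive two answers: an unadjusted p-value labelled as the assessment of the treatment effect, and an adjusted hazard ratio next to it. With 20,000 patients even a modest confounded difference can reach p < 0.05, and the two answers can point in different directions. Effectiveness is a stated aim, and the Introduction itself reports that an earlier registry linked TCM with higher recurrence. A crude p-value could not resolve that question.

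**Working it through.** The plan has no figure of its own to reproduce here. The 20,000 is a recruitment target taken from site volume, with no power calculation, and serves below only as N.

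**Inputs from the document:** N = 20,000; two-sided 0.05; TCM use of 83.1% in AIS and 42% in ICH (Introduction, earlier survey).

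**Assumptions, none of them in the document:** the two percentages are shares of patients and carry over to this registry; ICH makes up 20% of patients (range 10% to 30%); 12-month recurrence in AIS is 10% (also 5%); the ICH:AIS risk ratio runs from 0.5 to 2.0; follow-up is complete; TCM has no effect within either stroke type.

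**Step 1, imbalance of exposure.** Odds ratio of TCM use, AIS against ICH: (0.831/0.169) / (0.42/0.58) = 4.917/0.724 = 6.8.

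**Step 2, make-up of the groups at 20% ICH.**
- Users: 0.8 × 0.831 + 0.2 × 0.42 = 0.7488 of patients. Non-users: 0.2512.
- ICH among users: 0.084/0.7488 = 11.2%. ICH among non-users: 0.116/0.2512 = 46.2%.
- The standardised difference is 0.84 (0.63 to 0.95 for ICH shares of 10% to 30%).

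**Step 3, crude hazard ratio and rejection rate.** The risk in each group is the mixture of the two stroke-type risks. The crude HR is ln(1 − p_users)/ln(1 − p_non-users). The expected |z| is √(events × 0.7488 × 0.2512) × |ln HR| (Schoenfeld variance).

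Worked case, risk ratio 1.5 and AIS recurrence 10%:
- p_users = 0.888 × 0.10 + 0.112 × 0.15 = 0.1056
- p_non-users = 0.538 × 0.10 + 0.462 × 0.15 = 0.1231
- HR = 0.85; events = 20,000 × 0.11 = 2,200
- expected |z| = 20.34 × 0.163 = 3.31, so the test rejects about 91% of the time.

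| ICH:AIS risk ratio | Crude HR (AIS 10%) | Rejects, AIS 10% | Rejects, AIS 5% |
|---|---|---|---|
| 0.5 | 1.24 | 98% | 78% |
| 0.8 | 1.08 | 32% | 18% |
| 1.0 | 1.00 | 5% | 5% |
| 1.25 | 0.92 | 40% | 22% |
| 1.5 | 0.85 | 91% | 62% |
| 2.0 | 0.75 | 100% | 99% |

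At 10% AIS recurrence, the rate at a risk ratio of 1.5 is 53% with 10% ICH and 98% with 30% ICH. At a ratio of 1.25 it is 18% and 57%.

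**Step 4, simulation check** (400 runs per scenario, 20% ICH, 10% AIS recurrence, ratio set on the hazard scale):

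| ICH:AIS hazard ratio | Crude log-rank rejects | Stratified by stroke type |
|---|---|---|
| 0.5 | 95% | 5.3% |
| 1.0 | 7% | 7.5% |
| 1.5 | 91% | 4.3% |
| 2.0 | 100% | 3.3% |

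The four stratified rates average 5.1%. The Monte Carlo standard error of a 5% rate is √(0.05 × 0.95/400) = 1.1 points. Stroke type is the only confounder in this simulation, so the result does not show that stratifying by type alone would be enough in the registry.

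**The case against.** The strongest reply is that adjustment is already planned. The sentence after the log-rank statement provides for covariates and a propensity score, and the Cox model is itself a regression that this sentence can cover. This part stands: the plan does not rely on the log-rank test alone. A reader might infer that the confounded p-value would be the decisive one, but the section ranks no p-value and calls no result decisive. What remains is narrower: the text names one test for the treatment effect, that test is unadjusted, and the planned adjustment is not connected to it. This is a stated method, so it is not a detail left to the SAP that is not shown. The covariate list and the exact model can properly be left there.

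Other stronger readings are also not supported:
- **That the Introduction's figures show confounding.** They come from an earlier survey, are worded as shares of treatment, and concern exposure only. Confounding also needs outcome risk to differ by stroke type. The document gives neither those risks nor the AIS:ICH mix, and at equal risk there is no bias from this source.
- **That false rejection is nearly certain.** It depends on the unknown risk ratio. All-cause mortality would not be a better illustration, because it is a secondary outcome and the document gives no rates for it either.
- **That AIS and ICH will be pooled in the analysis.** The Statistical Analysis section does not say so; the two are recorded and classified separately.
- **That unadjusted tests are assigned to the mRS.** The Mann–Whitney and chi-square tests stand in a general list to be used as appropriate.
- **That the remark on clinical experience shows how TCM is chosen.** In context ("doctors will determine the treatment strategies based on their clinical experience") it concerns other routine treatments where guidelines offer nothing applicable. The sentence on syndrome differentiation is the better evidence.

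**Conclusion.** The point holds as a defect in a stated method. A plain log-rank test is named as the assessment of the treatment effect in a non-randomised comparison, and the adjusted regressions are not made the test. That conclusion rests on the text alone.

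The size is conditional. It depends on carrying the survey's percentages over to this registry and on the assumed ICH share, AIS recurrence and ICH:AIS risk ratio. In the scenarios examined, false rejection runs from the nominal 5% when recurrence risk is equal in the two types to nearly 100% when it differs twofold. The direction is also open: non-users contain more ICH, so TCM looks protective if ICH recurs more often and harmful if it recurs less often. Other differences between users and non-users, such as severity or age, are not in these figures and could add to or offset the bias.

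**What to change.** Reword the Statistical Analysis section so that the p-value and 95% CI for the treatment effect both come from the covariate- and propensity-score-adjusted Cox model, stratified by AIS/ICH. Describe the log-rank test and the Kaplan–Meier curves as descriptive.

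Apply the same rule to the other primary outcome. Any inference about a treatment effect on 3-month mRS should come from an adjusted ordinal model with age, admission NIHSS, pre-stroke mRS and stroke type, and unadjusted between-group tests should be descriptive only.

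Table 1 already lists all of these variables, so no new data are needed. The cost is wording in the protocol, with the SAP brought into line if it says the same, and the unadjusted p-value can no longer be the headline result.
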